### Concealment mechanism {16b}

Randomization will computer-generated via a secure website and can be accessed via an electronic device.

### Implementation {16c}

Participants will log in to a centralized monitoring service on the Navarrabiomed site through a secure website using a mobile electronic device. This process ensures that the trial is independent and secure.

## Assignment of interventions: blinding

### Who will be blinded {17a}

The assignment password will be kept in a confidential file in the Navarrabiomed center and will be opened at the end of the study’s analyses. To ensure masking, an alpha-numerical code will be assigned to each study group. This code will be delivered to the associated researcher and will not be revealed to the investigators in charge of processing the data until the analysis of the coded interventions is completed. Additionally, the researchers from the Navarrabiomed center will be responsible for preparing reports for the participants’ safety committee to verify the progress of the study. Following the conclusion of the baseline examination, the appropriate envelope will be opened by a study researcher, and the participants will be informed about their group allocation. Assessors of outcomes will be blinded to patient data, including allocation at baseline and follow-up. Blinding will be used for all specialized analyses. Owing to the nature of the study, patients cannot be blinded to the exercise training modality.

### Procedure for unblinding if needed {17b}

The design is open label with only outcome assessors being blinded, so unblinding will not occur.

### Data collection and management

#### Plans for assessment and collection of outcomes {18a}

The research staff will collect data on site, using questionnaires on secured Google Forms™ which will be assimilated in a password-protected Google drive™. All the parameters assessed in the study are defined a priori in a data dictionary elucidating standards for data collection.

#### Plans to promote participant retention and complete follow-up {18b}

Retention will be calculated as the number of participants who complete the entire 12-week training program divided by the total number of participants, also expressed as a percentage. A minimum adherence rate of 70% is considered satisfactory. Any data analysis disagreements will be resolved by a third-party biostatistician.

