### Intervention descriptions {11a}

Participants will be randomly assigned in a 1:1 ratio to one of two groups: the exercise group and the routine care group. The exercise group will undergo a 12-week exercise intervention, followed by a 12-week follow-up period. On the other hand, the routine care group will undergo a 12-week period of routine care, followed by a 12-week follow-up period. If participants are not engaging 2 times per week, the research team will reach out through email and/or phone to get a clear explanation as to why and to motivate the participants to continue. If the participants do not perform 70% of the training (or 17 out of 24 sessions), they will not be allowed to continue participation. The overall study procedure is illustrated in Fig. 1.

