**Fig. 1 Fig1:**
[figure not shown]
Flow of subjects through the “3, 2, 1 Move on Study.” Participants will be first randomly assigned to a 12-week period of standard daily routines (*n* = 40) or exercise training (*n* = 40). Both groups will be included in a 12-week follow-up period

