### Routine care group

Participants allocated to the control group will continue to receive routine care according to WHO international practice guidelines [13], followed by a 12-week follow-up period. These activities include engaging in physical education class at school and/or playing with friends at the park or in the backyard. To ensure adherence to the intervention, the research team will closely monitor participant engagement, reaching out to participants who are not logging in twice per week to understand the reasons for non-compliance and to provide motivation to continue. Participants who do not execute their training will not be allowed to continue with the study.

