## Assignment of interventions: allocation

### Sequence generation {16a}

Eligible participants will be randomly assigned to one of two groups using a computer-generated block randomization schedule (Research Randomizer V.4). Assignment will take place through previously constructed balanced blocks, which will allow equiprobable assignment and ensure that each group has the same number of participants. This allocation mechanism will be carried out until 84 total participants are assigned.

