## Statistical methods

### Statistical methods for primary and secondary outcomes {20a}

The study will adhere to the intention-to-treat principle and use the baseline observation carried forward imputation method, where missing data will be replaced by baseline values [39]. The final analysis population will be described and any differences from the enrolled population will be reported. Participants who drop out of the study may still be included in the analysis, although their data will provide less information and lower the estimated effects variance. Adherence will be measured as the number of completed sessions divided by the total number of sessions, expressed as a percentage. The first step of the analysis will be to calculate descriptive statistics for the overall sample and between groups. Since this is an experimental design with primary and secondary outcomes measured at three timepoints - baseline (t0 = week 0), post-intervention (t1 = week 12), and after a 12-week follow-up period (t2 = week 24) - for the two study groups (exercise and routine care), a comparative analysis between the measurements will determine the differences. A linear mixed model with repeated observations will be used for these comparisons, when appropriate, for each dependent variable. Subsequently, multivariate analysis will be carried out, and the autocorrelation between repeated measures will be taken into account. We will use longitudinal analysis methods, such as a generalized estimating equation approach, to control the differences among measurements at baseline and to incorporate incomplete observations into this analysis. Pearson correlations will be calculated between the maximal values of the primary and secondary outcomes. All analyses will be 2-sided and a significance level of *α* ≤ 0.05 will be used for the primary analysis.

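### Retention is divided over both arms although only one trains, so it cannot exceed 50%; the 70% adherence level is automatic if only continuing children are counted

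*Protocol article*

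**What the plan says.** Plans to promote participant retention and complete follow-up {18b} gives the formula: "Retention will be calculated as the number of participants who complete the entire 12-week training program divided by the total number of participants". The next sentence sets a level for a different quantity: "A minimum adherence rate of 70% is considered satisfactory".

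Adherence has its own definition under Statistical methods {20a}: "Adherence will be measured as the number of completed sessions divided by the total number of sessions, expressed as a percentage". No population is named there. The same section commits to intention to treat with baseline values carried forward, and allows dropouts to stay in the analysis.

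The design is set out under Intervention descriptions {11a}: "Participants will be randomly assigned in a 1:1 ratio to one of two groups: the exercise group and the routine care group". For the trained arm, "The exercise group will undergo a 12-week exercise intervention, followed by a 12-week follow-up period". For the other arm, the Routine care group section says: "Participants allocated to the control group will continue to receive routine care according to WHO international practice guidelines". Fig. 1 gives 40 children per arm. Sequence generation {16a} gives a larger total: "This allocation mechanism will be carried out until 84 total participants are assigned".

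Intervention descriptions {11a} also bars from further participation anyone who performs less than 70% of the training, put at 17 of 24 sessions. The Routine care group section repeats a removal rule for children who do not carry out their training, without a number.

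**The concern.** The retention formula pairs a numerator that only one arm can enter with a denominator that covers both. A routine-care child who attends every assessment never counts as retained. The formula is also silent on whether the primary outcome was measured and on the week-24 visit, so it does not describe complete follow-up, which is the subject of the section. Loss by arm matters here because the removal rule is tied to training that only one arm receives, and missing values are replaced by baseline values.

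The adherence problem is a different one. The level that counts as satisfactory is the same as the level below which a child is removed. Depending on who is counted, the criterion is either a real test or one that cannot be failed. Adherence to the exercise programme is among the things the Abstract says the study will evaluate, so the choice affects a reported result.

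**Working it through.** **Inputs.** Allocation is 1:1 ({11a}). Arms are 40 and 40 (Fig. 1), or 42 and 42 (Sample size {14}; total of 84 in {16a}). There are two sessions a week for 12 weeks (Exercise group section). The removal cut-off is 70%, or 17 of 24 sessions ({11a}). Assumed dropout is 10% ({14}).

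**1. The plan's own figure.** 12 × 2 = 24 sessions, and 0.70 × 24 = 16.8, rounded up to 17. 17/24 = 70.8% and 16/24 = 66.7%, so 17 of 24 is reproduced.

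**2. Ceiling of retention as written.** The maximum is exercise-arm n divided by total n: 40/80 = 50%, or 42/84 = 50%. This holds whether completing means doing all 24 sessions or staying to week 12.

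**3. Value at the assumed dropout.** If 10% of the exercise arm does not complete, 0.90 × 40/80 = 45%, and 0.90 × 42/84 = 45%. Over the exercise arm alone the same children give 36/40 = 90%.

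**4. What the figure cannot register.** With 36 exercise completers and a denominator of 80, the result is 45% whether none or all 40 of the routine-care children are lost. It is also unchanged by how many children return at week 24.

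**5. Adherence by population.** Let f be the share of the exercise arm removed, s the mean sessions those children completed, and a the mean sessions of those who continue. The protocol gives none of these, so the values below are assumptions.

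- Continuing children only: a/24. The removal rule forces a ≥ 17, so this is at least 70.8%.
- All children randomised to exercise: [f·s + (1 − f)·a]/24.

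| f | s | a | Continuing only | All randomised to exercise |
|---|---|---|---|---|
| 0% | – | 24 | 100% | 24/24 = 100% |
| 10% | 8 | 20 | 83.3% | (0.8 + 18.0)/24 = 78.3% |
| 10% | 8 | 17 | 70.8% | (0.8 + 15.3)/24 = 67.1% |
| 20% | 8 | 17 | 70.8% | (1.6 + 13.6)/24 = 63.3% |
| 30% | 0 | 20 | 83.3% | (0 + 14.0)/24 = 58.3% |
| 50% | 0 | 17 | 70.8% | (0 + 8.5)/24 = 35.4% |

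The first column of results never falls below 70%. The second does in four of the six rows, including one with only 10% removed.

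**The case against.** Four arguments can be made for the plan.

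First, the authors may have meant participants in the programme when they wrote the retention denominator. That is a plausible intention, but the text does not say it. Elsewhere the article uses the word total for both arms together, as in 80 children or 84 assigned.

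Second, a reader might infer that the 70% adherence criterion is met by construction, whatever happens. The documents do not support that. The adherence definition is not restricted to children who continue, and the intention-to-treat statement with its wording on dropouts lets removed children count. The criterion is automatic only in the continuing set. This part of the objection stands and limits the point to an unspecified population.

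Third, a reader might set the 50% ceiling against the 70% level and conclude that retention is bound to fail its own target. The 70% follows the retention formula directly, but the text attaches it to adherence. No retention target is stated, so the comparison should not be made. The placement is confusing and worth tidying.

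Fourth, retention is not listed among the trial's outcomes, no feasibility conclusion is planned, and neither quantity enters the primary comparison of MVPA. The article also promises to describe the analysis population and its differences from those enrolled, and detail on attrition by arm may sit in a fuller document. All of that is fair and keeps the importance modest. It does not rescue a formula that is printed and gives the wrong figure if followed.

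**Conclusion.** The point holds in two limited parts. As written, retention cannot exceed 50% and is half the exercise-arm completion rate: 45% instead of 90% at the assumed dropout, taking dropout to mean not completing the programme. It carries no information on loss in the routine-care arm or at week 24. This rests only on the literal wording and the 1:1 allocation, and both candidate totals give the same result.

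The 70% adherence level is uninformative if adherence is calculated among continuing children. It is a real criterion if all children randomised to exercise are counted, where the illustrative scenarios run from 35.4% to 100%. The protocol leaves the choice open. The primary treatment comparison is not directly affected.

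**What to change.** - Define retention separately for each arm, as randomised children with a valid primary outcome at T1 divided by children randomised to that arm, and give the same figure separately for T2.
- Report completion of the training programme as its own quantity, over the exercise arm only.
- Define adherence as sessions completed divided by 24, over all children randomised to exercise, counting sessions after removal or stopping as not completed. Judge the 70% level on that figure only, and move the sentence that states it next to the adherence definition.
- Reconcile the removal rule in Intervention descriptions {11a}, its repetition in the Routine care group section, and the intention-to-treat statement in {20a}. The documents should state how removed children are followed and counted, and how a rule about training can apply to an arm that has none.

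The definitions take a few sentences and use data already being collected. The price is that reported adherence may be less favourable than a figure restricted to children who continue.

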### Data management {19}

Data will be entered directly into access database, via a secure web platform for building and managing online databases, by Navarrabiomed using a password-protected computer. All data retained will be in an electronic, re-identifiable format. Paper-based/non-electronic data (e.g., data collection instruments) will be transferred to an electronic format and all paper-based/non-electronic data will be destroyed.

### Confidentiality {27}

All participants will be assigned a study-specific identification number. Exported data will be de-identified and stored separately from the dataset containing participant identifying information (only the participant’s unique study number is contained in both files for the purpose of re-identification). Any study information will be stored on a password-protected computer or secure Navarrabiomed applications accessible only by the research team.

### Plans for collection, laboratory evaluation, and storage of biological specimens for genetic or molecular analysis in this trial/future use {33}

No biological specimens will be collected as part of this trial.

## Statistical methods

### Statistical methods for primary and secondary outcomes {20a}

The study will adhere to the intention-to-treat principle and use the baseline observation carried forward imputation method, where missing data will be replaced by baseline values [39]. The final analysis population will be described and any differences from the enrolled population will be reported. Participants who drop out of the study may still be included in the analysis, although their data will provide less information and lower the estimated effects variance. Adherence will be measured as the number of completed sessions divided by the total number of sessions, expressed as a percentage. The first step of the analysis will be to calculate descriptive statistics for the overall sample and between groups. Since this is an experimental design with primary and secondary outcomes measured at three timepoints - baseline (t0 = week 0), post-intervention (t1 = week 12), and after a 12-week follow-up period (t2 = week 24) - for the two study groups (exercise and routine care), a comparative analysis between the measurements will determine the differences. A linear mixed model with repeated observations will be used for these comparisons, when appropriate, for each dependent variable. Subsequently, multivariate analysis will be carried out, and the autocorrelation between repeated measures will be taken into account. We will use longitudinal analysis methods, such as a generalized estimating equation approach, to control the differences among measurements at baseline and to incorporate incomplete observations into this analysis. Pearson correlations will be calculated between the maximal values of the primary and secondary outcomes. All analyses will be 2-sided and a significance level of *α* ≤ 0.05 will be used for the primary analysis.

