### Sample size {14}

There was some evidence to suggest that physical activity interventions [37] led to an improvement in the proportion of children who engaged in MVPA during scholar day (odds ratio (OR) 2.74, 95% confidence interval (CI), 2.01 to 3.75). Study parameters are as follows: alpha = 0.05, power = 0.80, delta =  − 1.37 (OR difference with control group). After adjustment for an estimated 10% estimated dropout rate (a similar rate has been observed in previous systematic reviews [38]), 42 participants per group will be needed for sufficient power (difference in the mean daily MVPA between groups of ± 5 min) at follow-up.

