### Methods in analysis to handle protocol non-adherence and any statistical methods to handle missing data {20c}

The potential effects of missing data will be explored under various models for nonignorable missing data mechanisms and through multiple imputation models under ignorable missing data assumptions [40].

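### Carrying baseline values forward as the main missing-data rule contradicts the planned mixed model and GEE, dilutes a true effect, and adds bias if loss differs between arms

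*Protocol article*

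**What the plan says.** Section {20a} covers primary and secondary outcomes together. It pairs intention to treat with a rule for missing values: the study will "use the baseline observation carried forward imputation method, where missing data will be replaced by baseline values". It then says of children who drop out that "their data will provide less information and lower the estimated effects variance".

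For the comparison of the two arms over weeks 0, 12 and 24 it states: "A linear mixed model with repeated observations will be used for these comparisons, when appropriate, for each dependent variable". It adds a GEE approach, in part "to incorporate incomplete observations into this analysis".

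Section {20c} says: "The potential effects of missing data will be explored under various models for nonignorable missing data mechanisms". A second route is named in the same sentence, namely "through multiple imputation models under ignorable missing data assumptions". The verb there is explore. Nothing in {20c} replaces the rule in {20a}.

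Three other places bear on the point. The sample size section {14} assumes 10% dropout, 42 per group and a 5-minute difference in daily MVPA. The intervention description {11a} ends participation for children who complete fewer than 17 of 24 sessions. The routine care section also prints a removal rule for children who do not do their training, although that arm has no training programme.

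**The concern.** **Contradiction.** A mixed model or GEE is chosen so that a child with a missing visit still contributes the visits that were observed. Filling every missing follow-up with the baseline value removes the incompleteness that those models are meant to handle. The two approaches give different estimates, and {20a} does not say which one yields the primary result.

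**Bias.** The rule assumes that a child who leaves is exactly at baseline at weeks 12 and 24. That gives the child no programme effect and no change with age or season. Many secondary outcomes here (height, weight, fitness, motor competence, executive function) can be expected to change over 24 weeks at age 4 to 5.

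**Precision.** Single imputation treats filled-in values as measured. Less information should mean a larger variance, yet {20a} says the variance falls.

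At stake are the primary MVPA estimate and every repeated secondary outcome.

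**Working it through.** **Inputs from the protocol article.** 42 per group, 10% dropout and a 5-minute difference ({14}); two-sided alpha 0.05 ({14}, {20a}); removal below 17 of 24 sessions ({11a}).

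**Inputs not given, so assumed.** Outcome SD, baseline-to-follow-up correlation, change without intervention (g), and loss by arm other than 10%. The article calls 70% adherence satisfactory ({18b}), so 30% loss serves as an upper scenario.

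**The plan's own figure.** The article gives no figure for the effect of the imputation rule. Its 42 per group does not follow from the stated odds ratio. A 5-minute difference gives 42 only with an SD near 7.7 minutes: 37 evaluable per group implies 5 / [(1.960 + 0.842) x sqrt(2/37)] = 7.68, and 37/0.9 = 41.1, rounded up to 42. That is a separate matter; 42 is used here only as the group size.

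**Expected estimate.** Let delta be the true effect, and dE and dC the loss in the exercise and routine care arms. Assume leavers would have had the same effect as completers. Then

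E = (1 - dE)(delta + g) - (1 - dC)g = (1 - dE)delta - (dE - dC)g.

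For the 5-minute target:
- 10%/10% loss: 0.9 x 5 = 4.5 min, whatever g is.
- 30%/30% loss: 0.7 x 5 = 3.5 min.
- 30%/10% loss, g = 0: 3.5 min.
- 30%/10% loss, g = 5 min: 3.5 - 0.2 x 5 = 2.5 min.

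**Simulation in SD units.** 42 per arm, baseline-adjusted, correlation 0.6, loss completely at random, 4,000 trials per scenario:

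| True effect | g | Loss E/C | Formula | Baseline carried forward | Observed data only |
|---|---|---|---|---|---|
| 0 | 0.5 | 10%/10% | 0 | type I error 4.9% | |
| 0 | 1.0 | 10%/10% | 0 | type I error 5.0% | |
| 0 | 0.5 | 15%/10% | -0.025 | type I error 5.2% | |
| 0 | 0.5 | 30%/10% | -0.10 | type I error 9.4% | about 5% |
| 0 | 1.0 | 30%/10% | -0.20 | type I error 20% | about 5% |
| 0.5 | 0.5 | 10%/10% | 0.45 | 0.446, power 70.5% | 0.498, power 75.4% |
| 0.5 | 0 | 30%/10% | 0.35 | 0.35, power 56% | unbiased, power 70% |
| 0.5 | 0.5 | 30%/10% | 0.25 | 0.25, power 29% | unbiased, power 70% |

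A separate run of 1,500 trials gave type I errors of 10.3% and 18% for the two 30%/10% null rows.

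**Standard error.** For a mean change m with SD of change s and loss d, the variance after carrying baseline forward is proportional to (1 - d)s² + d(1 - d)m². From observed values only it is s²/(1 - d). The first is smaller while m² < s²(2 - d)/(1 - d)²:
- d = 0.10: m < sqrt(1.9/0.81) s = 1.53 s.
- d = 0.30: m < sqrt(1.7/0.49) s = 1.86 s.

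This is a guide for unadjusted change. In the baseline-adjusted simulation at 10%/10% loss, the SE was 0.169 against 0.185 with no gain (1 - 0.169/0.185 = 9% smaller). With a 0.5 SD effect it was 0.188 against 0.185 at g = 1.0 SD and 0.224 against 0.185 at g = 2.0 SD. The direction therefore reverses when growth is strong.

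**The case against.** The strongest reply concerns what counts as the truth. The attenuation figures credit leavers with the full benefit. If children removed for not training gain nothing, the intention-to-treat effect at 30% exercise-arm loss is 0.7 x 0.5 = 0.35 SD. With no maturation, carrying baseline forward then gives 0.347 (coverage 94.7%), while the observed-data model gives 0.496 (coverage 88%). With 0.5 SD maturation the first is 0.10 too low and the second 0.15 too high. This stands: the mixed model is valid only under missing at random, and removal driven by adherence may violate that.

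Stronger readings that a reader might infer, and that the documents do not support:
- **Type I error rises for any outcome that matures with age.** It does so only if loss differs between arms. The only rate in the article is 10%, with no split by arm, and a removal rule is printed for both arms.
- **Error bars are too narrow in general.** The model SE after carrying baseline forward matches that estimator's own sampling SD (0.171 against 0.172 in one run). It is small only relative to what the observed data support, and only when change is modest. The excess type I error comes from bias.
- **Imputed values are systematically too low.** For MVPA the sign of g is unknown; the background section {6a} cites falling preschool activity. A decline of 0.5 SD turns the 30%/10% bias to +0.10 SD. For timed runs, improvement means a lower value.
- **No incomplete records remain at all.** A missing baseline cannot be filled by this rule, so the accurate statement is that essentially no incomplete follow-up remains.
- **The variance sentence is a deliberate claim.** It may be a slip. It needs correcting either way.

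Section {20c} is real mitigation, since its methods could expose dependence on the rule. As exploration, they leave the main result as it is.

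**Conclusion.** The point holds in a limited form. Section {20a} fixes a main imputation rule that defeats the purpose it gives for its own models, and its statement about variance is wrong as written. A statistical analysis plan that is not shown would not cure this, because the protocol article itself names the rule.

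If leavers would have had the completers' effect, a true effect is diluted by the exercise-arm loss. At the planned 10% this is modest: 5 becomes 4.5 minutes, or 0.50 becomes 0.45 SD, with power about 70% instead of 75% when g is 0.5 SD. The larger figures (null bias -0.10 SD, type I error about 10%) need unequal loss and a non-zero g. The 30%/10% split and g = 0.5 SD are assumptions. The session rule makes unequal loss plausible but gives no rate. A non-zero g is likely for maturing secondary outcomes and of unknown sign for MVPA. General claims of inflated type I error or understated standard errors are not supported.

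**What to change.** 1. In {20a}, name one primary analysis: the linear mixed model already planned, fitted to all observed values without imputation, with arm by visit and adjustment for baseline. State that it is valid under missing at random.
2. Remove carrying baseline forward as the main rule. It may stay as one sensitivity analysis at most.
3. Delete or correct the sentence on the variance of the effect.
4. Keep the {20c} multiple imputation and non-ignorable models as named sensitivity analyses. Include delta-adjusted versions, one of which assumes no benefit in leavers, because adherence-driven removal may breach missing at random.
5. Keep outcome collection going, so that less has to be assumed about children who leave. This concerns data collection only; the removal rule itself is not judged here.

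The cost is a short protocol amendment, which under {25} needs ethics approval before implementation and a registry update if it counts as important. It should be settled before allocation is revealed to the analysts. The statistical price is that the primary result then relies on missing at random, which is why item 4 cannot be dropped.
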